## Abstract

**Background::**

Polycystic ovary syndrome (PCOS) is a female endocrine disease with a high incidence. At present, drug treatment is still the main therapeutic strategy for PCOS. Traditional Chinese medicine has a long history in the treatment of menstrual disorders. Shouwu Jiangqi Decoction (SWJQD) is a traditional herbal medicine prescribed in a clinical setting as a remedy for PCOS. Acupuncture also plays an important role in regulating the menstrual cycle and treating PCOS. This study aims to examine the efficacy and safety of the combination of SWJQD and acupuncture in the treatment of PCOS.

**Methods::**

This randomized controlled trial will be conducted with a total of 81 participants diagnosed with PCOS. The participants will be randomly divided into 3 treatment groups: group A will receive SWJQD combined with acupuncture; group B, SWJQD combined with sham acupuncture; and group C, metformin. Each treatment will last 3 months. The primary outcomes include the Homeostatic Model Assessment of Insulin Resistance (HOMA-IR) index and the Oral Glucose Tolerance Test. The secondary outcome measures include sex hormone levels, body mass index, ovulation rate, clinical pregnancy rate, and complete genome sequencing data. Adverse events will be recorded during the intervention and follow-up.

**Results::**

This study will investigate whether the combination of SWJQD and acupuncture can alleviate the clinical symptoms and improve insulin resistance in patients with PCOS. The results of this study are expected to provide clinical evidence for the application of the combination of SWJQD and acupuncture in patients with PCOS.

**Trial registration::**

Chinese Clinical Trial Registry: ChiCTR1900028106, ChiMCT1900002826 (registered on December 12, 2019).

## Introduction

1

Polycystic ovary syndrome (PCOS) is a common female reproductive disease that mainly occurs in adolescents and at a childbearing age.^[1]^ The clinical manifestations are persistent anovulation, scanty ovulation, insulin resistance (IR), excessive androgen secretion and polycystic changes in the ovary, leading to irregular menstruation and infertility.^[2]^ The pathogenesis of PCOS is still unclear. It is currently believed that it may be related to genetic, environmental, or mental health factors, as well as other comprehensive factors.^[3–5]^

Epidemiological studies have confirmed that PCOS is a serious gynecological disease with a high incidence in China and across the globe.^[6,7]^ PCOS patients have high risk of type 2 diabetes, obesity, hypertension, metabolic syndrome, and cardiovascular disease.^[8]^ Due to the endocrine and metabolic nature of the disorder, PCOS patients may have some difficulty with fertility, as well as be experiencing severe physical and psychological distress.^[9,10]^

Recent studies have revealed that inflammation and obesity are important factors in the pathophysiological basis of PCOS, while both hyperandrogenemia and IR have established key roles in its development.^[4,11]^ In 1980, Burghen et al first proposed that IR is a major clinical characteristic of PCOS.^[12]^ In the next several decades, several researches have confirmed that there is a close relationship between PCOS and IR.^[13]^ Any abnormality in the insulin signaling pathway can lead to IR. The mechanism of IR is related to disordered post-insulin receptor signal transduction, particularly involving the phosphatidylinositol trikinase signaling pathway.^[4]^

At present, the main aim of the routine treatment of PCOS is to improve IR, reduce hyperandrogenemia and thus induce ovulation as the main therapeutic target by lifestyle and drug intervention.^[14]^ Improving endocrine function and inducing ovulation is an important way to improve the pregnancy rate among infertile patients with PCOS.^[15,16]^ Surgical and assisted reproductive techniques are used as second-line therapies to assist the pregnancy.^[17]^

Studies have found that acupuncture can regulate the reproductive endocrine function of PCOS patients through multiple signaling pathways and targets in the hypothalamus-pituitary-gonadal/adrenal axis,^[18]^ thus treating PCOS and improving local symptoms such as hairy acne.^[19,20]^

Traditional Chinese medicine also has certain advantages in regulating female endocrine function, hormone level and menstruation.^[18,21]^ Animal research has confirmed that Shouwu Jiangqi Decoction (SWJQD) has potent therapeutic effects in the rat model PCOS-IR by correcting defective insulin signaling transduction.^[22]^

Therefore, in this study we will try to combine the advantages of traditional Chinese medicine and acupuncture in the treatment of PCOS. To achieve this, we will carry out a standardized clinical trial to improve the treatment plan and evaluation criteria, and provide an objective theoretical basis and methodology for the treatment of PCOS by acupuncture combined with SWJQD.

## Methods and study design

2

### Objective

2.1

The purpose of this study is to assess the clinical efficacy of SWJQD combined with acupuncture in the treatment of PCOS.

### Overall study design

2.2

This is a randomized controlled trial to investigate the clinical effect of SWJQD combined with acupuncture in improving the insulin sensitivity and regulation of sex hormones in Chinese women with PCOS compared with metformin. The study period will include 3 months of pharmacological interventions, acupuncture and a follow-up visit. The general design of this study is demonstrated in Figure 1 and Table 1.

**Figure 1 F1:**
[figure not shown]
Flowchart of the study procedure.

**Table 1 T1:**
[figure not shown]
Schedule of enrollment, intervention, and assessment.

### Study setting

2.3

Chinese women diagnosed with PCOS will be enrolled at the Department of Reproduction, Zhangjiagang TCM Hospital Affiliated to Nanjing University of Chinese Medicine, China. The recruitment will begin in January 2020 and is expected to be completed in March 2022.

### Inclusion criteria

2.4

The inclusion criteria for the participants are as follows:

(1)Chinese women aged 18 to 35 years.(2)Body mass index (BMI) between 24 to 32 kg/m^2^.^[23,24]^(3)Traditional Chinese medicine syndrome differentiation: kidney deficiency, phlegm and blood stasisness.(4)Satisfying the Rotterdam PCOS diagnostic criteria in adults, including at least 2 of the 3 biochemical or clinical hyperandrogenism characteristics^[25,26]^: (a) Irregular cycles and ovulatory dysfunction (an intermenstrual interval >35 or <21 days or <8 cycles per year) or amenorrhea (>90 days for any 1 cycle), (b) clinical and/or hyperandrogenism: Clinical hyperandrogenism on the Chinese Mainland: Ferriman-Gallwey (FG) score ≥5^[27,28]^; biochemical hyperandrogenism: total testosterone (T) >2.6 nmol/l and free testosterone ≥6.0 pg/ml,^[29]^ (c) polycystic ovarian morphology (the threshold for PCOM should be on either ovary, a follicle number per ovary of >20 and/or an ovarian volume ≥10 ml, ensuring no corpora lutea, cysts or dominant follicles are present.(5)Presence of IR. The criteria of IR is defined by the homeostatic model assessment (HOMA-IR) index ([fasting serum insulin (μU/ml) × fasting blood glucose (mmol/l)] / 22.5). A value ≥2.14 is considered to be indicative of IR.^[30]^(6)No birth planning in the future 3 months.(7)Being able to follow the plan of treatment, examination, and follow-up.(8)Being able to fully understand and voluntarily sign informed consent.

### Exclusion criteria

2.5

The exclusion criteria for the participants consist of:

(1)Presence of abnormal liver and kidney functions(2)Presence of any other endocrine disorders such as:(a)uncorrected thyroid disease(b)type 1 or 2 diabetes mellitus or hypertension(c)Cushing's syndrome(d)Congenital adrenal hyperplasia(e)Suspected androgen-secreting adrenal or ovarian tumor.(3)History of alcoholism, malignant tumors, epilepsy, or mental disorders.(4)History of coronary heart disease, severe arrhythmia, cardiopulmonary insufficiency, or cardiac stenting procedure.(5)Use of a pacemaker, hearing aid, or any other device with electronic or metal components.(6)Presence of infectious diseases and severe skin lesions.(7)Pregnant or lactating state.(8)Unable to cooperate with the research caused by other diseases or reasons;(9)Use of hormonal or other medication including Chinese herbal prescriptions, which may affect the outcome of the last 2 months.(10)History of receiving acupuncture treatment in the past 2 months.

### Interventions

2.6

After baseline measurements, patients satisfying the inclusion criteria will be randomly divided into 1 of the 3 treatment groups, as shown below:

1.Group A: SWJQD combined with acupuncture for 3 months.2.Group B: SWJQD combined with sham acupuncture for 3 months.3.Group C: Metformin at a dose of 500 mg 3 times/day for 3 months.

All the participants will be instructed to return to visit the doctor every week.

#### Shouwu Jiangqi Decoction

2.6.1

The SWJQD consists of 10 g of Fallopia multiflora, 12 g of Radix Puerariae, 15 g of Batryticated silkworm, 15 g of Astragalus propinquus Schischkin, 15 g of Dioscorea oppositifolia L., 10 g of Euonymus alatus, 10 g of Cyperus rotundus L., and 10 g of Cuscutae Semen. The traditional Chinese medicine doctor will prescribe the formula according to the clinical symptoms of the participants. Each decoction should be taken twice a day, except during the menstrual period. The SWJQD intervention will last for 3 months.

#### Acupuncture

2.6.2

The acupoint selection for the acupuncture group will be as follows: Zhongji (RN3), Guanyun (RN4), Zigong (EX-CA1), Sanyinjiao (SP6), Zhongwan (RN12), Tianshu (ST25), Fenglong (ST40), Zusanli (ST36), and Qihai (RN6). Needles (40 mm in length, 0.3 mm in diameter; Hwato Brand, Suzhou Medical Appliance Factory, China) will be inserted into all acupoints (to a depth of 25–30 mm). Following lifting, thrusting, and stimulating until ’de qi’, the needles will be left in the acupoints for 30 minutes before removal. This acupuncture intervention will be conducted for 3 months, except during the menstrual period.

#### Sham acupuncture

2.6.3

The acupoint selection for sham acupuncture will be: sham Zhongji (RN3), Guanyun (RN4), Zigong (EX-CA1), Sanyinjiao (SP6), Zhongwan (RN12), Tianshu (ST25), Fenglong (ST40), Zusanli (ST36), and Qihai (RN6), which are 1 cun outward to Zhongji (RN3), Guanyun (RN4), Zigong (EX-CA1), Sanyinjiao (SP6), Zhongwan (RN12), Tianshu (ST25), Fenglong (ST40), Zusanli (ST36), and Qihai (RN6), respectively. Needles (15 × 0.3 mm) will be inserted to 2 to 3 mm at the sham acupoints. The sham acupuncture intervention duration will be the same as that for the acupuncture group.

#### Metformin

2.6.4

In order to reduce the gastrointestinal effects of metformin, the oral dose will be increased gradually as 500 mg per day during the first week, 1000 mg per day during the second week, and 1500 mg per day in the third week and will be maintained at the dose of 500 mg 3 times daily (at morning, noon, and night) from the fourth week onwards, for a total of 3 months.

### Outcome measures

2.7

#### Primary outcomes

2.7.1

The clinical effectiveness of 3 months of (A) SWJQD combined with acupuncture, (B) SWJQD combined with sham acupuncture, and (C) metformin for the improvement of IR will be assessed and determined by the HOMA-IR index (calculated from fasting glucose and serum insulin) and the Oral Glucose Tolerance Test.

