### Sample size calculation

2.8

The most important outcome in this study is fasting serum insulin. Sample size was estimated based on the above primary outcome measures. The target sample size calculated by PASS 11.0 is a total of 63 participants (21 participants in the Group A, 21 participants in the Group B, 21 participants in the Group C). This result was based on a power calculation using a 5% significance level, 90% power, and current knowledge of the average serum insulin level. By enrolling 27 participants in each group, we can allow a drop-out rate of 20%.

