### Randomization and allocation concealment

2.10

Eligible participants will be allocated to the three groups in a 1:1:1 ratio by an investigator according to a random sequence generated by a computer. The random number assignment will be generated by an independent statistician who will not be a member of the research team. The random number will be placed in sealed, opaque envelopes and assigned by a staff, who will not be a member of the clinical trial team and participating in data collection. When new participants are enrolled in the study, the doctor will open the envelopes in sequence and assign participants to the corresponding intervention accordingly. All processes will be recorded and saved as appropriate.

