### Statistical methods

2.13

The data of all participants will be involved in the final statistical analysis according to the intent-to-treat principle. The data statisticians will be blinded to the group allocation. All statistical analyses will be performed in SPSS software v19.0 and a *P* value <.05 will be considered statistically significant.

The continuous variables, such as participants’ biochemical and hormonal profiles including estradiol, luteinizing hormone, follicle-stimulating hormone, prolactin, testosterone, progesterone, dehydroandrosterone, sex hormone binding globulin, body mass index, waist-to-hip ratio, FG score, ovulation rate, clinical pregnancy rate, and early abortion rate will be presented as mean ± SD. Between-group comparisons will be carried out on changes from baseline to after treatment using ANOVA or its non-parametric equivalents. Group comparisons will be carried out using the Kruskal-Wallis test followed by Mann-Whitney *U* test.

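### Two primary outcomes without a success rule, a third quantity behind the sample size, and a flat P<.05 across three arms put the primary error rate above 5% if success on either outcome counts

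*Protocol article*

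**What the plan says.** **Primary outcomes.** The abstract states: "The primary outcomes include the Homeostatic Model Assessment of Insulin Resistance (HOMA-IR) index and the Oral Glucose Tolerance Test". Section 2.7.1 gives the same pair: "the HOMA-IR index (calculated from fasting glucose and serum insulin) and the Oral Glucose Tolerance Test". Neither place says whether one success is enough or both are needed. Neither names the OGTT analyte, time point or summary.

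**Sample size.** Section 2.8 opens with "The most important outcome in this study is fasting serum insulin" and continues "Sample size was estimated based on the above primary outcome measures". Fasting insulin is an ingredient of HOMA-IR but is not one of the two listed primary outcomes.

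**Arms and comparator.** Under Section 2.10 participants are "allocated to the three groups in a 1:1:1 ratio". Section 2.2 describes the aim as "improving the insulin sensitivity and regulation of sex hormones in Chinese women with PCOS compared with metformin", which points to A vs C. Group B, with sham needling, serves a different question, A vs B.

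**Analysis.** Section 2.13 sets one threshold for all analyses, a P "value <.05 will be considered statistically significant". Changes from baseline are compared across the groups by ANOVA or a rank equivalent, and "Group comparisons will be carried out using the Kruskal-Wallis test followed by Mann-Whitney" U tests. No contrast is given priority, and the text does not say whether the pairwise tests depend on the three-group result.

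**The concern.** A reader cannot tell from these sections which result would make the trial positive. Three quantities compete for primary status: HOMA-IR, the OGTT and fasting insulin. Two different questions are built into the arms: the combination against metformin, and real against sham needling. A three-group test answers neither directly, and it can be significant because of B vs C alone.

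With a flat P<.05, each extra route to a positive claim raises the overall false positive rate above the nominal 5%, unless the success rule prevents it. The choice of outcome and contrast could also be made after the data are seen. Each further OGTT time point or analyte treated as primary would add to this.

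**Working it through.** **Inputs from the protocol.** Two primary outcomes (Section 2.7.1); three arms, 1:1:1 (2.10); 0.05 per test (2.13; sidedness not stated, two-sided assumed); 5% significance, 90% power, 21 evaluable and 27 enrolled per arm, 20% drop-out (2.8).

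**Assumptions.** Normal outcomes, no true difference between any arms on either outcome, and correlation ρ between the two outcomes from 0 to 0.9. The protocol gives no ρ. HOMA-IR and the OGTT may share fasting glucose, so high values are plausible.

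**Step 1: the protocol's own figure.** 21 / (1 − 0.20) = 26.25, rounded up to 27 per arm, 81 in all. The drop-out step reproduces. The 63 cannot be reproduced, because no difference, SD or test is given. Solved backwards for two groups, d = (1.960 + 1.282) × √(2/21) ≈ 1.00 (1.03 with the t distribution). For a three-group ANOVA it implies f ≈ 0.46.

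**Step 2: one contrast, two outcomes, either suffices.** With independent outcomes, 1 − 0.95² = 0.0975. Simulated for A vs C alone: 0.0953 at ρ = 0 and 0.0712 at ρ = 0.9. The rate therefore exceeds 5% before the third arm is considered.

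**Step 3: three arms, two outcomes, either suffices.** 60,000 simulated trials per ρ, 21 per arm, ANOVA and pairwise t tests:

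| ρ | pairwise only after a significant three-group test | pairwise regardless |
|---|---|---|
| 0 | 0.0973 | 0.2266 |
| 0.3 | 0.0944 | 0.2197 |
| 0.5 | 0.0931 | 0.2156 |
| 0.7 | 0.0845 | 0.1973 |
| 0.8 | 0.0794 | 0.1827 |
| 0.9 | 0.0708 | 0.1661 |

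For a single outcome the rate is about 0.05 gated and 0.12 ungated. A check with Kruskal-Wallis and Mann-Whitney (4,000 trials) gave 0.096 and 0.235 at ρ = 0, and 0.087 and 0.207 at ρ = 0.5. The naive figure for six independent tests, 1 − 0.95⁶ = 0.265, is too high because pairwise tests share arms.

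**Step 4: both outcomes required.** The probability that both are significant cannot exceed that of either one alone, so it is at most about 5% for a gated family. At ρ = 0.9 under the global null it is 2 × 0.0488 − 0.0708 = 0.027 gated and 2 × 0.1197 − 0.1661 = 0.073 ungated. In the ungated case the excess comes from the three pairs, not from the second outcome.

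**Step 5: price of splitting alpha instead.** Assume d ≈ 1.00, so d / √(2/21) ≈ 3.24. At 0.025 per outcome for one contrast, power is Φ(3.24 − 2.24) ≈ 84%. Restoring 90% takes 25 evaluable per arm; 25 / 0.8 = 31.25, so 32 enrolled per arm and 96 in all. Bonferroni over all six tests (0.0083) gives Φ(3.24 − 2.64) ≈ 73%. Restoring 90% takes 31 evaluable per arm; 31 / 0.8 = 38.75, so 39 enrolled per arm and 117 in all.

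**The case against.** **This is an article, and the detail may sit elsewhere.** A testing order, an alpha rule or the OGTT variable could be in a full protocol or SAP that is not shown. This stands for the OGTT variable taken alone. It does not dispose of the point, because the article commits itself to two primary outcomes, to a different most important outcome, and to one threshold for all analyses. Those statements conflict, or give the wrong error rate, as written.

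**The pairwise step reads as a gate.** Kruskal-Wallis followed by Mann-Whitney is the usual wording for post hoc testing. With three arms a gate holds each outcome near 5%. This is the more natural reading, so a reader who infers that the plan runs a 20% or higher error rate goes too far: that figure needs pairwise tests run regardless of the three-group result. The text leaves this possible but does not favour it.

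**Both outcomes may be required.** Section 2.7.1 joins them with a plain conjunction. If that means joint success, the second outcome adds no inflation. The protocol does not say so.

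**Metformin is named as the comparator.** Correct, in Section 2.2. It would be wrong to say that the protocol gives no hint of a main comparison. What is missing is any sentence in the outcome or analysis sections that gives A vs C priority.

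**A null A vs C result might be read as parity with metformin.** A reader might fear this, but the protocol makes no equivalence or non-inferiority claim, and its discussion asks whether the combination is more effective. It is not part of this point.

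**Conclusion.** The point holds in a limited form. The protocol names two primary outcomes without a success rule, ties its sample size to a third quantity, and applies P<.05 to all tests of three arms without ranking the contrasts.

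If success on either outcome counts, the false positive rate under the global null is about 7-10% with gated pairwise tests and about 17-23% with ungated ones. These are not figures that the protocol fixes. They depend on the assumed outcome correlation (0.9 to 0), 21 evaluable per arm and two-sided tests. If both outcomes must succeed and the pairwise tests are gated, the rate is no more than about 5%. The defect is that the text permits all of these readings.

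A reader might also infer that settling on HOMA-IR and A vs C leaves the 90% power intact. The protocol does not support this. The calculation refers to fasting insulin and gives no difference, SD or test, so the power for HOMA-IR A vs C is unknown.

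**What to change.** Before unblinding, amend the protocol or SAP as follows:

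1. Name HOMA-IR at month 3 as the single primary outcome, and rewrite Section 2.8 so that its most important outcome agrees.
2. Make the OGTT a key secondary outcome with one named variable. If both are to stay primary, state that both must succeed, or use Holm across the two.
3. Make A vs C, the comparison in Section 2.2, the primary contrast at two-sided 5%. Test A vs B only if A vs C is significant. Treat B vs C as descriptive.
4. Report every contrast with a 95% CI.
5. State the difference, SD and test behind the 63, and recheck power for HOMA-IR A vs C.

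**Cost.** The wording change is small, and the first contrast keeps the full 5%, so the testing order itself spends no alpha. Whether 27 per arm is enough for the new primary analysis stays open until item 5 is done. The OGTT and B vs C lose primary status. The sham comparison can be confirmed only if the combination first beats an active drug, so a real needling effect could go unconfirmed. The investigators should accept that order knowingly.

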#### Secondary outcomes

2.7.2

(1)Sex hormone profile, including estradiol, luteinizing hormone, follicle-stimulating hormone, prolactin, testosterone, progesterone, dehydroandrosterone, and sex hormone binding globulin levels measured on the 2nd to 3rd day of menstruation, before and after the intervention.(2)BMI (weight/(height)^2^); waist-to-hip ratio (waist circumference/hip circumference), and FG score measured before and after the intervention.(3)Ovulation rate in every menstrual period.(4)Clinical pregnancy rate, and early abortion rate in the 9 months follow-up.(5)Complete genome sequencing of each group before and after the treatment.(6)Security index tests, including routine blood, liver function, kidney function, and blood lipid tests respectively before and after the intervention.(7)Investigators will contact subjects weekly by WeChat message or phone call to record the adverse reactions and side effects in this trial.

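### Ovulation is defined per menstrual period, so a woman with no period during the 3-month treatment has no value instead of counting as not ovulating

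*Protocol article*

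**What the plan says.** Section 2.7.2 (Secondary outcomes) gives the ovulation outcome as "Ovulation rate in every menstrual period". In the same list the sex hormone panel is "measured on the 2nd to 3rd day of menstruation, before and after the intervention".

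Section 2.4 (Inclusion criteria) counts as irregular cycles "an intermenstrual interval >35 or <21 days or <8 cycles per year", or "amenorrhea (>90 days for any 1 cycle". Irregular cycles are one of three diagnostic features, and a woman qualifies by "including at least 2 of the 3".

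The abstract states "Each treatment will last 3 months". Section 2.13 (Statistical methods) states "The data of all participants will be involved in the final statistical analysis according to the intent-to-treat principle". It also puts the ovulation rate among the continuous variables, summarised by mean and SD.

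The article does not say how a woman without a period is counted for ovulation, or when her post-treatment hormone sample is taken.

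**The concern.** The unit of the ovulation outcome is the menstrual period, and periods happen after randomisation. The abstract credits acupuncture with a role in regulating the menstrual cycle, and the introduction names induction of ovulation as a main aim of treatment. The number of periods a woman has is therefore part of the treatment response.

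A rate built on periods looks only at the cycles that occurred. A woman who stays without menses for the 3 months leaves the comparison when she should count against her arm. The arms are then compared among women, and among cycles, selected by response. That is not a comparison of the groups as randomised, which section 2.13 promises. It also gives more weight to women who resume cycling if periods are pooled.

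The hormone panel has a milder form of the same problem. Its post-treatment sample waits for menses, so a woman without menses has either no value or a late one.

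**Working it through.** The article gives no ovulation figure to reproduce. The only nearby figure is the arm size used below: 21/(1 - 0.20) = 26.25, rounded up to 27 per group, and 3 × 27 = 81. This agrees with section 2.8 and the abstract.

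**Step 1. Can an eligible woman have no period in the window?** Inputs are the cycle lengths in section 2.4 and a treatment of 3 months, taken as 90 days. With regular cycles of length L, the expected number of onsets is 90/L. If the window starts at a random point of the cycle, the chance of no onset is max(0, 1 - 90/L).

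| Cycle length L (days) | Expected onsets in 90 days | Chance of none |
|---|---|---|
| 35 | 2.57 | 0 |
| 45.6 (365/8, the limit of 8 cycles a year) | 1.97 | 0 |
| 90 | 1.0 | 0 |
| 120 | 0.75 | 0.25 |

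The 120-day cycle is an example of a cycle above the 90-day limit. If treatment instead starts straight after a day 2 baseline sample, as the hormone timing suggests, the next onset in a 120-day cycle comes about 120 - 2 = 118 days later, outside the window. So an empty window is possible under the article's own criteria, but only for cycles longer than about 90 days.

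**Step 2. What does the outcome do with her?** If periods are pooled, she adds 0 to the numerator and 0 to the denominator. If each woman has her own rate, hers is 0/0, which is undefined. Either way she has no effect on the result.

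**Step 3. How much can this hide?** Illustration with assumed inputs: 27 women in an arm, m of whom have no period, while the others have 3 periods each, 2 of them ovulatory.

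- Per period: 2(27 - m) / [3(27 - m)] = 2/3, whatever m is.
- Per 30-day interval over all women: 2(27 - m) / (27 × 3).
- Ovulations per woman: 2(27 - m) / 27.
- Any ovulation: (27 - m) / 27.

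| m | Women with a per-period value | Per period | Per 30-day interval, all 27 | Ovulations per woman | Any ovulation |
|---|---|---|---|---|---|
| 0 | 27 | 66.7% | 66.7% | 2.00 | 100% |
| 3 | 24 | 66.7% | 59.3% | 1.78 | 88.9% |
| 5 | 22 | 66.7% | 54.3% | 1.63 | 81.5% |
| 8 | 19 | 66.7% | 46.9% | 1.41 | 70.4% |
| 10 | 17 | 66.7% | 42.0% | 1.26 | 63.0% |

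The per-period rate cannot register a failure to resume cycling. The three measures over all women can.

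**Step 4. Hormone sample.** With treatment ending at a random point of a regular cycle, the mean wait for the next onset is L/2 and the maximum is L. The mean is about 18 days for a 35-day cycle, 23 for 45.6, 45 for 90 and 60 for 120.

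**The case against.** The outcome is a single line in a list, and it may only mean that ovulation is assessed in each cycle. The mean and SD summary suggests one value per woman, not a pooled count. Rules for women without menses, visit windows and missing values are commonly left to the full protocol, which is not shown. Eligibility is also milder than it first looks. One cycle over 90 days is enough, so ongoing amenorrhoea is not required. Irregular cycles are only one of three features, and cycles under 21 days also qualify. A baseline sample on day 2-3 implies a recent period at entry.

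Most of this limits the size of the problem without removing it. One value per woman is still undefined when she has had no period, and reading period as cycle leaves the same gap. The objection is to a unit that the article does state, not to a detail left out.

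A reader might infer that the per-period rate will rank the arms wrongly. Such a case can be built with 10 women per arm. In one arm 5 women have 3 ovulatory cycles and 5 have no menses. In the other all have 3 cycles, of which 70% are ovulatory. Per period this gives 15/15 = 100% against 21/30 = 70%; per woman-month it gives 15/30 = 50% against 21/30 = 70%. No figure in the article supports those inputs, so the reversal is shown to be possible, not likely.

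A reader might also infer that hormone values will be missing in exactly the non-responders. The article does not support that either: the sample may be late and not missing, and the number of women affected is unknown.

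**Conclusion.** The concern holds for the ovulation outcome. Its stated unit depends on an event after randomisation that the treatments aim to change, and a woman with no period in the 3 months is left without a value despite the all-participants analysis. This rests on two assumptions: that some enrolled women will have a cycle longer than about 90 days during treatment, which the criteria allow, and that no rule elsewhere assigns them a value.

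The size of the bias cannot be computed, because the article gives neither the share of such women nor the expected ovulation rates. The tables show the mechanism only. The hormone panel has a related but lesser limitation. Both are secondary outcomes; HOMA-IR and the Oral Glucose Tolerance Test are not tied to menses. The change is worth making, but the trial's main conclusion does not depend on it.

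**What to change.** Define ovulation per randomised woman over the fixed 3-month treatment window, with two measures: any ovulation (yes or no) and the number of ovulations per woman. Keep women without menses in the denominator, counted as having no ovulation unless ovulation or pregnancy was documented. Report the per-period rate only as a descriptive supplement.

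For the hormone panel, keep the day 2-3 sample. Report by arm the number of women without one and the time from end of treatment to sampling. Do not substitute samples taken at any cycle phase, and do not exclude luteal samples. The first would make cycle phase differ between women who resumed menses and those who did not; the second would select on ovulation. Both bring response-dependent differences into the comparison.

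The cost is a change of outcome wording and two extra items in the report. The small downside is that a late ovulation that goes undetected may be counted as none. The article does not say how ovulation is detected, so it should be confirmed that detection does not itself wait for a period.
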